### 2.5. Eligibility Criteria

Inclusion criteria will be: (1) participants aged 60 years or older; (2) participants currently enrolled in the UNATI/UNISUAM program; and (3) preserved cognitive function screened using the Mini-Mental State Examination (MMSE), adopting education-adjusted cut-off scores appropriate for the Brazilian population, in order to ensure that participants are able to understand the study procedures and complete the proposed questionnaires [21]. Participants will be excluded if they present functional limitations or medical conditions that may compromise their health or confound study outcomes; report a history of neurological disease; report any acute episode of dizziness; present abnormal fluid accumulation (edema), especially in the lower limbs; have severe visual impairment; present clinical conditions that prevent the performance of SVT, such as the presence of a cardiac pacemaker, recent lower limb surgery (within the past year), a history of deep vein thrombosis, or previous hip or knee arthroplasty; have a diagnosis of rheumatoid arthritis; use a walking assistive device; or have undergone spinal arthrodesis.

### 2.6. Randomization, Allocation, Blinding and Implementation Procedures

Participants will be randomly allocated using a computer-generated randomization sequence (https://www.random.org). The randomization system will include 192 allocations, each linked to one of three colors representing the intervention groups (blue, black, and red), corresponding to Groups A, B, and C. Allocation will be concealed using sequentially numbered, opaque, sealed envelopes, which will be opened only after completion of the initial assessments. The randomization sequence and allocation concealment procedures will be managed by a researcher not involved in outcome assessment or statistical analysis.

Participants will be informed that the study compares different intervention strategies that may provide therapeutic benefits, and that they may or may not perceive vibratory stimuli during the intervention. Due to the perceptible nature of the vibration stimulus and the absence of a sham-vibration condition, participant blinding cannot be fully guaranteed.

After the initial assessments are completed, the initial assessor (Examiner 1) will leave the testing area to remain unaware of group allocation. A licensed physiotherapist (Examiner 2), with specific training and experience in SVT, will then enter the testing area and apply the intervention according to the assigned randomized condition. Examiner 2 will remain unaware of baseline and post-intervention outcome data. After the intervention is completed, Examiner 2 will leave the room, and Examiner 1 will return to conduct the post-intervention assessments using the same standardized procedures applied during the initial assessment.

To evaluate blinding/expectancy, after completion of post-intervention assessments, participants will be asked to indicate which condition they believe they received (SVT vs. no SVT) and to rate their confidence in this judgment.

### 2.7. Criteria for Discontinuing Allocated Interventions

Adverse events will be systematically monitored before, during, and after each intervention session. Participants will be asked about symptoms such as dizziness, nausea, pain, excessive fatigue, discomfort, or any other unexpected symptoms. All adverse events will be recorded on a standardized form, including the type of event, severity, duration, need for clinical assistance, and possible relationship to the intervention. In the presence of moderate or severe adverse events, the session will be interrupted, and the participant will be referred for appropriate clinical evaluation.

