A total of 192 older adults enrolled in the Open University for the Elderly (UNATI) at Centro Universitário Augusto Motta (UNISUAM), Bonsucesso Unit, will be recruited. Participants will be allocated in a 1:1:1 ratio into three groups using sequentially numbered, opaque, sealed envelopes prepared from a computer-generated randomization list. The allocation sequence will be implemented after completion of baseline assessments to preserve allocation concealment. In the control group (Group A), participants will be considered a usual physical activity control group. Participants allocated to this group will continue their regular activities offered by the UNATI/UNISUAM program, including light walking, stretching exercises, activities of daily living, and recreational cognitive activities. No additional vibration stimulus or sham-vibration procedure will be applied. Therefore, the study will compare systemic vibratory therapy combined with habitual physical activity in two distinct positions versus habitual physical activity alone. In the semi-squat intervention group (Group B), participants will engage in the same routine activities and, 30 min after the end of their UNATI sessions, will be directed to the Laboratory of Musculoskeletal Performance of the Graduate Program in Rehabilitation Sciences (PPGCR/UNISUAM), where SVT will be performed in a semi-squat position with knees flexed at 120°. To ensure positioning consistency, the platform base will be pre-marked to standardize foot placement. The intervention will use mechanical vibration at F of 15, 20, and 25 Hz with a D of 5 mm, corresponding to peak accelerations (Apeak) of 2.3 g, 4.1 g, and 6.4 g. Each frequency will be applied for 1 min, with a 1 min rest interval between frequencies, in a cycle repeated three times, totaling 18 min per session. Interventions will occur twice weekly, for a total of 10 sessions. All sessions will be conducted by a research assistant trained in the operation of the vibration platform. Systemic vibratory therapy will be delivered using a Kikos P204IXC alternating oscillatory vibration platform (manufacturer is Kikos) manufactured in São Paulo, Brazil.

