### 2.4. Recruitment

The sample will be recruited intentionally and by convenience and opportunity at the Open University for Seniors (UNATI) of the Augusto Motta University Center (UNISUAM). Although participants are recruited from the UNATI/UNISUAM program, the research procedures will always be conducted by a research team independent of the regular UNATI team, as well as those responsible for routine activities.

Baseline characteristics will include sociodemographic data, history of falls, and level of physical activity. Previous falls will be recorded based on the FES-I and self-report over the past 12 months. Physical activity level will be assessed at baseline using the International Physical Activity Questionnaire (IPAQ) [20]. These variables will be described by group and considered in the interpretation of baseline comparability and potential confounding factors.

The UNATI team will not participate in randomization, allocation concealment, outcome assessment, intervention application, or statistical analysis. To minimize cross-contamination between groups, intervention sessions will be scheduled separately, and participants will be instructed not to share details of the procedures to which they were allocated with other participants during the study period. The study will be conducted at the Musculoskeletal Performance Laboratory, linked to the Postgraduate Program in Rehabilitation Sciences (PPGCR/UNISUAM), located at [name].

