### 2.9. Interventions

The protocol will be performed by a trained physiotherapist who is unaware of the initial assessment and will be conducted in accordance with the requirements of the Model for Description and Replication of Interventions TIDieR [22].

In the control condition, participants will continue their routine activities offered by the UNATI/UNISUAM program and will only undergo the scheduled clinical, sociodemographic, and outcome assessments. This group will be considered a usual physical activity control group, without additional vibration stimulus or sham-vibration procedures.

Semi-squat intervention group: Participants will perform their routine activities from the UNATI/UNISUAM program and SVT in a semi-squat position (knee flexion at 120°) using the following biomechanical parameters: F = 15, 20, and 25 Hz and D = 5 mm, Apeak of 2.3 g; 4.1 g and 6.4 g. The participant will perform 1 min of vibration in each D position (D = 5 mm) with 1 min of rest between each, repeating 3 times, totaling 18 min of intervention in a total of 10 interventions, twice a week. For standardization of the D position, the base of the vibration will be marked beforehand where participants should keep their feet during the sessions. SVT will be performed at least 30 min after their activities proposed by the UNATI/UNISUAM program.

Seated intervention group: Participants will perform the routine activities of the UNATI/UNISUAM and SVT programs while seated in a chair with their hands resting on their knees. The biomechanical parameters will be the same as those reported for the semi-squat position.

Adherence to the intervention will be monitored using individual attendance logs completed at each session by the research team. The number of completed sessions, missed sessions, and reasons for absence, when available, will be recorded. Adherence will be expressed as the percentage of completed sessions relative to the total number of planned sessions. Participants who complete at least 80% of the planned sessions will be considered adherent to the intervention protocol.

Below is a flow diagram (Figure 1) of the progress through the phases of a randomized trial of three groups (that is, enrolment, intervention allocation, follow-up, and data analysis).

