We expect that SVT combined with physical activity may contribute to improvements in physical fitness, mobility, and postural control, supporting the need to identify safer and more effective protocols for older adults [34,38].

This study has some limitations that should be acknowledged. First, the absence of a sham-vibration condition limits the ability to fully blind participants and does not allow complete control for nonspecific contextual effects related to device contact, time, and exposure to the laboratory environment. Second, recruitment by convenience from a single institutional program may limit the external validity of the findings. Third, although strategies will be adopted to reduce contamination between groups, participants belong to the same university-based program, which may allow exchange of information between them. Finally, the relatively short intervention period may limit the magnitude of changes in patient-centered outcomes such as concern about falling.

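### As written, adverse events are asked about only around vibration sessions, so harms cannot be compared between SVT and control; separately, no arm has a stated measure of the shared activity after baseline

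*Protocol article*

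**What the plan says.** **Adverse events.** Section 2.7 states: "Adverse events will be systematically monitored before, during, and after each intervention session". Participants are asked about dizziness, nausea, pain, fatigue, discomfort and other unexpected symptoms. A standard form records severity, duration and possible relationship to the intervention. No other time for asking is given.

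**Control contacts.** Section 2.1 says of Group A: "No additional vibration stimulus or sham-vibration procedure will be applied". Section 2.9 adds that control participants "will only undergo the scheduled clinical, sociodemographic, and outcome assessments". The fixed assessment sequence in Section 2.1 is the FES-I, the march test, surface EMG and posturography.

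**Vibration sessions.** For the SVT groups, "Interventions will occur twice weekly, for a total of 10 sessions" (Section 2.1; Group C receives the same vibration parameters).

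**Exposure to activity.** Section 2.9: "Adherence to the intervention will be monitored using individual attendance logs completed at each session by the research team"; and "Adherence will be expressed as the percentage of completed sessions relative to the total number of planned sessions". Section 2.4: "Physical activity level will be assessed at baseline using the International Physical Activity Questionnaire (IPAQ". No later measurement of activity is stated.

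**The concern.** The symptoms on the list occur in people aged 60 and over whether or not they stand or sit on a vibrating platform. If they are solicited only where vibration is given, background symptoms are recorded in Groups B and C alone. The resulting counts could make SVT look harmful. Equally, a real excess could be dismissed because there is no control rate to set it against. The judgement of possible relationship to the intervention would also be made without a background rate. The Discussion presents the work as "supporting the need to identify safer and more effective protocols for older adults", so readers will look for a safety comparison.

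The second part is a separate matter. The trial contrasts SVT plus habitual activity with habitual activity alone. That contrast isolates SVT only if habitual activity stays similar between arms during the trial. Participants are not fully blinded, so activity could change differently by arm, and the plan states no measure that would show it.

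**Working it through.** The plan gives no figure of its own on this point, so the check is a count of stated contacts per arm, followed by an illustration under assumed rates.

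**1. Adverse-event enquiries per participant**
- Enquiry points per session (Section 2.7): before, during, after = 3.
- Planned sessions (Section 2.1): 10 in B, 10 in C, 0 in A.
- Enquiries = points × sessions: B = 3 × 10 = 30; C = 3 × 10 = 30; A = 3 × 0 = 0.
- Period covered: 10 sessions ÷ 2 per week = 5 weeks.

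B and C have the same schedule, so those two arms can be compared.

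**2. Attendance and activity**
- Adherence = completed sessions ÷ planned sessions. The only planned number is 10, so the 80% rule in Section 2.9 means 0.80 × 10 = 8 sessions. In A the denominator is 0 and the rule does not apply. That is reasonable for adherence to SVT, but it means the log says nothing about the activities that all arms share.
- IPAQ: stated at baseline, not after. Stated post-baseline activity measures: none in A, B or C.
- The UNATI activities are run by a team separate from the research team that keeps the logs (Section 2.4).

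**3. Size of the possible artefact**

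Assumptions: 64 participants per arm (the recruitment target), the same true symptom risk p in every arm, events captured in full in B and not at all in A. The documents give no value of p, so a range is shown. Expected number in B = 64 × p. With 0 of 64 in A, Fisher's exact two-sided test gives p = 0.058 for 5 events in B and p = 0.028 for 6. The last column is therefore P(X ≥ 6) with X ~ Binomial(64, p).

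| Assumed risk, all arms | Expected in B | Recorded in A | Chance of a spurious nominal p < 0.05, B vs A |
|---|---|---|---|
| 5% | 3.2 | 0 | 0.10 |
| 10% | 6.4 | 0 | 0.63 |
| 20% | 12.8 | 0 | 0.99 |
| 30% | 19.2 | 0 | > 0.99 |

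The same holds for C versus A. The plan does not propose this test. The table only shows how large a difference the asymmetric asking could produce by itself.

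**The case against.** The strongest reply is that this is a journal article, that Section 2.7 does not say events are asked about at sessions and nowhere else, and that the control assessments include an unspecified clinical one. Safety is not a listed outcome, no adverse-event test is planned, and the section exists to trigger interruption and referral. Part of this stands. Events volunteered by controls could be noted, so the zero in the table is zero solicited, not a proof that none would be recorded. But the article does more than stay silent: it fixes a session-based schedule and restricts control contacts to assessments. Even if the clinical assessment included symptoms, it would not be comparable with questioning at every session.

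A reader might also infer four stronger things that the documents do not support:
- That harms cannot be compared between any arms. B and C share a schedule and can be.
- That falls are asked about in the SVT groups but not in control. Section 2.7 does not name falls for any arm; fall history is taken at baseline from everyone.
- That SVT visits raise attendance at UNATI activities. Nothing in the text shows this. All participants are already enrolled, and the SVT groups follow the same routine.
- That the missing activity measure is a defect of the control arm. It is missing in all three arms.

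**Conclusion.** The point holds in a limited form. Under the stated rule, SVT participants have up to 30 scheduled adverse-event enquiries and control participants have none, so the plan supports a harms comparison of B with C but not of SVT with control. How misleading the counts would be depends on the background symptom risk, which the documents do not give. Across assumed risks of 5% to 30%, the artefact runs from about 3 to about 19 participants of 64 in each SVT group, against none solicited in control.

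Separately, similarity of habitual activity between arms during the trial cannot be checked from the measurements stated. This does not show that activity will differ.

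Neither part changes the sample size or the primary FES-I analysis. Both deserve correction before enrolment, because the missing data cannot be recovered afterwards on equal terms.

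**What to change.** Leave the session-by-session monitoring as it is, for safety management. In addition:

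1. At the existing post-intervention visit, give all three groups one identical adverse-event form that covers the whole intervention period and includes falls.
2. Have it completed after the FES-I and the other outcome assessments, alongside the question on which condition participants believe they received. Examiner 1 should not see it, because reports of vibration-related symptoms could reveal allocation.
3. Base SVT-versus-control safety tables on that form only. Report the session records separately, for B and C.
4. Repeat the IPAQ at the same visit and report it by group. Add UNATI attendance by group if the programme's registers are available.

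The visit already takes place, so the cost is a few minutes per participant and one extra form. A weekly form at UNATI activities would be more sensitive, but those are not research contacts: the UNATI team takes no part in outcome assessment. The main downside is that recall over about 5 weeks will miss some minor symptoms that session questioning would catch. It asks every arm the same questions over the same period, however, and the comparison with control needs that.

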### 2.8. Ancillary and Post-Trial Care

Participants who experience any type of harm related to their participation in the study will receive complementary post-trial assistance, such as necessary clinical treatment for immediate adverse effects related to trial procedures, at no cost. In addition, all participants will have guaranteed access to physiotherapy care after the trial is completed.

### 2.9. Interventions

The protocol will be performed by a trained physiotherapist who is unaware of the initial assessment and will be conducted in accordance with the requirements of the Model for Description and Replication of Interventions TIDieR [22].

In the control condition, participants will continue their routine activities offered by the UNATI/UNISUAM program and will only undergo the scheduled clinical, sociodemographic, and outcome assessments. This group will be considered a usual physical activity control group, without additional vibration stimulus or sham-vibration procedures.

Semi-squat intervention group: Participants will perform their routine activities from the UNATI/UNISUAM program and SVT in a semi-squat position (knee flexion at 120°) using the following biomechanical parameters: F = 15, 20, and 25 Hz and D = 5 mm, Apeak of 2.3 g; 4.1 g and 6.4 g. The participant will perform 1 min of vibration in each D position (D = 5 mm) with 1 min of rest between each, repeating 3 times, totaling 18 min of intervention in a total of 10 interventions, twice a week. For standardization of the D position, the base of the vibration will be marked beforehand where participants should keep their feet during the sessions. SVT will be performed at least 30 min after their activities proposed by the UNATI/UNISUAM program.

Seated intervention group: Participants will perform the routine activities of the UNATI/UNISUAM and SVT programs while seated in a chair with their hands resting on their knees. The biomechanical parameters will be the same as those reported for the semi-squat position.

Adherence to the intervention will be monitored using individual attendance logs completed at each session by the research team. The number of completed sessions, missed sessions, and reasons for absence, when available, will be recorded. Adherence will be expressed as the percentage of completed sessions relative to the total number of planned sessions. Participants who complete at least 80% of the planned sessions will be considered adherent to the intervention protocol.

Below is a flow diagram (Figure 1) of the progress through the phases of a randomized trial of three groups (that is, enrolment, intervention allocation, follow-up, and data analysis).

### 2.10. Outcome Measures

The primary outcome will be concern about falling, assessed using the Falls Efficacy Scale-International, Brazilian version (FES-I-Brazil). Secondary outcomes will include functional physical conditioning, electromyographic activity, muscle synergism, and center of pressure oscillation.

### 2.11. Concern About Falling

Concern about falling will be assessed using the Falls Efficacy Scale-International, Brazilian version (FES-I-Brazil). This questionnaire presents questions about the perception of fear of falling when performing 16 activities. Each activity has a score from one to four, with 1 point (not at all concerned), 2 points (slightly concerned), 3 points (moderately concerned), and 4 points (extremely concerned). The total score can range from 16 to 19 points (low concern), 20 to 27 points (moderate concern), and 28 to 64 points (high concern). This instrument will be administered at baseline and within 48 h after the final intervention session [16,17,18]. In addition to analyzing FES-I as a continuous outcome within the planned Group × Time framework, interpretability will be supported by reporting the proportion of participants who shift across established concern categories (low/moderate/high) from baseline to post-intervention. Because MCID/MID thresholds for patient-reported outcomes can vary substantially across estimation methods and populations, and because credible anchor-based MIDs are not consistently available for community-dwelling older adults, the study will also apply a transparent distribution-based benchmark (0.5 baseline SD) to describe a minimal important change in FES-I as a supplementary interpretive reference rather than a substitute for the primary inferential model [23,24]. This approach is intended to strengthen clinical interpretability while avoiding overstatement of “clinical significance” in the absence of stable, population-specific anchor-based thresholds.

### 2.12. Physical Conditioning

Physical conditioning will be assessed using the 2 min stationary march test, which consists of performing the following task: the participant is instructed to perform a stationary march for 2 min, alternately raising their knees to a height marked between the midpoint of the patella and the anterior superior iliac spine (ASIS). The participant is instructed to maintain a constant pace while being stimulated by the evaluator every 30 s to perform the task, with the 2 min time being recorded. The participant may stop performing the movements if necessary and resume during the execution time, but the timer will continue running, and the evaluator will monitor and count the complete elevations of one knee (right) during the execution of the test. If the patient has any balance deficit, a support may be used. The result is given by the total count of elevations of one knee (right) for 2 min; the classification is given according to the average total number of steps according to age. In men aged 60 to 64, a performance of between 87 and 115 steps is expected; between 65 and 69 years, between 86 and 116 steps; from 70 to 74 years, between 80 and 110 steps; from 75 to 79 years, between 73 and 104 steps; from 80 to 84 years, between 71 and 103 steps; from 85 to 89 years, between 59 and 91 steps; and from 90 to 94 years, between 52 and 86 steps. For women, the reference values are slightly lower: 75 to 107 steps (60–64 years), 73 to 106 (65–69 years), 68 to 101 (70–74 years), 66 to 98 (75–79 years), 60 to 90 (80–84 years), 50 to 88 (85–89 years), and 44 to 81 (90–94 years) [25]. Interpretation of test performance is based on comparison with these normative values. Results below the expected range indicate lower functional endurance and poorer physical conditioning, possibly reflecting impairments in the cardiorespiratory system and overall mobility. On the other hand, values within or above the average for the participant’s age and sex suggest a good level of physical fitness, indicating greater functional capacity and a lower risk of physical decline.

